### **27.7 Dosing**

In this study anakinra subcutaneous (SC) will be administered at a dose level of 100 mg SC once daily. Anakinra will be administered every other day in patients who have severe renal insufficiency or end stage renal disease (defined as creatinine clearance < 30 mL/min as estimated from serum creatinine levels).

**Dose will be increased to 200 mg SC once daily**, with a maximum dose limit of 8 mg/kg/day, at **Week +8** if the change in at least one of the two most bothersome outcomes selected by the parents/guardians at the Day 1 visit has not improved by  $\geq$  the MCID as defined in Section 9.1. If the MCID is not achieved after 8 weeks on maximum trial dose of 200mg (max dose 8 mg/kg/day), **treatment with anakinra may be discontinued after a review and discussion between the study PI and subject's parent(s) of their child's individual results from all study outcome measures.**

**Dose will be increased to 200 mg SC once daily**, with a maximum dose limit of 8 mg/kg/day, at **Week +16** if the change in at least one of the two most bothersome outcomes selected by the parents/guardians at the Day +1 visit have worsened by  $\geq$  the MCID as defined in Section 9.1 between week +8 and week +16, after an improvement from Day +1 to week +8. If the MCID is not achieved after 8 weeks on maximum trial dose of 200mg (max dose 8 mg/kg/day), **treatment with anakinra may be discontinued after a review and discussion between the study PI and subject's parent(s) of their child's individual results from all study outcome measures.**

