**For example:**

- At week +8, if a subject has not improved in the chosen items then the dose will be increased to 200 mg SC daily.
- At week +8, if a subject has improved, then the dose stays at 100 mg SC daily. However, if this individual then has worsening of the two most bothersome outcomes from week +8 to week +16, after improving from day 1 to week +8, the dose will be increased to 200 mg SC daily at that point (i.e. increase at week +16 after not increasing at week +8).

**Dose will be decreased by 50 mg SC once daily** at any time throughout the study if a participant develops any of the following:

- Neutropenia  $<1200$  cells/microliter persistent for  $\geq 2$  weeks
- Thrombocytopenia  $<50 \times 10^9$  platelets/liter persistent for  $\geq 2$  weeks
- Mild/moderate hypersensitivity reactions including urticaria, rash, and pruritis
- Participants develops a CTCAE grade 3 AE

**Anakinra will be stopped** if the AE above does not resolve within 2 weeks of decreasing the dose by 50 mg SC once daily. Anakinra will be restarted at 0.5 times the last dose administered once the AE is resolved. If the AE recurs with restarting anakinra, it will be discontinued and the subject monitored per protocol.

The starting dose is the same dose level as recommended for adult rheumatoid arthritis patients. The dose escalation is within the range of the recommended dose in Neonatal onset multisystem inflammatory disease (NOMID), including also pediatric patients, is related to body-weight, with a recommended starting dose of 1-2 mg/kg up to a maximum dose of 8 mg/kg.

Smaller children with lower body weight need higher dose levels/kg body-weight in order to achieve similar anakinra serum exposure as in older, heavier children, due to a higher capacity to eliminate anakinra/kg body-weight, based on pharmacokinetic data in 22

systemic-onset juvenile idiopathic arthritis (SJIA) pediatric patients in the age range 2-17 years.

As an example, based on this study, a patient with a body-weight of 20 kg is predicted to require a dose of 4 mg/kg/day to achieve similar anakinra exposure (area under the curve [AUC]0-24h, ss and Cmin, ss) as a dose of 100 mg in a 50 kg patient. Additional examples are given below:

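### Section 27.7 orders escalation to 200 mg at Week +8 on symptom outcomes alone and does not exempt a child whose dose was already cut or restarted for an adverse event that has since resolved.

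*Protocol*

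**What the plan says.** Section 27.7 starts every child at 100 mg once daily, apart from an every-other-day schedule in severe renal impairment. At Week +8 the dose is to rise to 200 mg when "the change in at least one of the two most bothersome outcomes selected by the parents/guardians at the Day 1 visit has not improved", improvement being a gain of at least the MCID. The limit attached to the order is "with a maximum dose limit of 8 mg/kg/day". The worked example repeats it: "At week +8, if a subject has not improved in the chosen items then the dose will be increased to 200 mg SC daily". Section 9.1 (Phase 2 primary endpoint) states the same outcome-driven rule and refers back to Section 27.7.

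A second escalation point, at Week +16, applies when a chosen outcome worsens by at least the MCID "between week +8 and week +16, after an improvement from Day +1 to week +8".

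Section 27.7 then gives the safety rules:

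- The dose is cut by 50 mg "at any time throughout the study if a participant develops any of the following". The triggers are persistent neutropenia, persistent thrombocytopenia, mild or moderate hypersensitivity, and any grade 3 event.
- The drug is stopped "if the AE above does not resolve within 2 weeks of decreasing the dose".
- "Anakinra will be restarted at 0.5 times the last dose administered once the AE is resolved".
- If the event comes back after the restart, the drug is discontinued.

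Footnote e to the Schedule of Events (Section 10.2) names escalation and decrease together, gives no order between them, and points to Section 27.7.

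**The concern.** The escalation order is worded as mandatory and depends only on symptom scores. It does not ask whether the child tolerated 100 mg, whether a cut has already been made, or whether the investigator thinks an increase is safe. By contrast, the same paragraphs do allow a review between investigator and parents before the drug is discontinued for lack of effect at 200 mg.

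The decrease, stop and restart rules do not fill the gap. They say what happens when an event occurs, but not whether the reduced dose is kept once it resolves, nor whether a reduced or restarted child leaves the escalation scheme. Read literally, two sets of instructions apply to the same child, and one of them takes the dose above the level that produced the event.

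What is at stake is the safety of children, and of adults unable to consent, who receive daily injections at home from their parents.

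**Working it through.** The protocol states no figure for this point, so there is none to reproduce. The check is a reading of the rules in sequence, followed by dose arithmetic.

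**Inputs, all from Section 27.7:** starting dose 100 mg; escalated dose 200 mg; cap 8 mg/kg/day; decrease 50 mg; restart factor 0.5; stop deadline 2 weeks after the cut. The 20 kg weight is one of the protocol's own examples. The 15 kg and 25 kg weights are illustrative.

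**Step 1: the child's dose before Week +8.**

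- Cut once, event resolved: 100 − 50 = 50 mg.
- Cut, not resolved in 2 weeks, stopped, then resolved and restarted: 0.5 × 50 = 25 mg. This fits before the visit: a cut at Week +3, a stop at 3 + 2 = Week +5, resolution and restart at Week +6.

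**Step 2: the dose ordered at Week +8 if the MCID is missed.** Ordered dose = min(200, 8 × weight in kg). It does not depend on the dose the child is on.

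| Weight | 8 × weight | Ordered dose | Ratio to the 100 mg at which the event arose |
|---|---|---|---|
| 12.5 kg | 100 mg | 100 mg | 1.0 |
| 15 kg | 120 mg | 120 mg | 1.2 |
| 20 kg | 160 mg | 160 mg | 1.6 |
| 25 kg | 200 mg | 200 mg | 2.0 |
| above 25 kg | above 200 mg | 200 mg | 2.0 |

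The cap keeps the order at or below 100 mg only at 100 / 8 = 12.5 kg or less.

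**Step 3: does exposure follow dose?** In the Section 27.7 table, a 50 kg patient has a predicted steady-state AUC of 18,776 ng·h/mL at 100 mg and 37,552 at 200 mg, and 37,552 / 18,776 = 2.0. On the protocol's own prediction, doubling the dose doubles exposure.

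**Step 4: does any other text block the order?**

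- Section 14.0 discontinues the drug for liver-injury criteria, serious infection, malignancy and severe hypersensitivity. Persistent neutropenia, persistent thrombocytopenia and mild or moderate hypersensitivity, which trigger the decrease, are not on that list.
- Section 13.4 allows the study to be terminated. It sets no condition on an individual's escalation.
- Section 13.0, item 6, withdraws a child who cannot safely tolerate participation. A child whose event resolved at a lower dose is not clearly in that position.
- The reference to a tolerated dose in Section 9.1 belongs to the secondary endpoints and is not a dosing condition.
- Discontinuation on recurrence after restart acts only once the child has been re-exposed. It does not govern whether to escalate.

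**Step 5: an event still active at Week +8.** If it is unresolved 2 weeks after the cut, the drug is stopped and there is no current dose to raise. A direct clash between decrease and escalation is therefore confined to a cut made within roughly the 2 weeks before the visit.

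**The case against.** The strongest reply is that the decrease rule runs throughout the study while escalation happens at two fixed visits, so the continuing safety rule naturally governs. The protocol also discontinues the drug on recurrence, the escalated dose stays within the 8 mg/kg maximum it cites for another paediatric indication, and a sensible investigator would not double the dose of a child just reduced for toxicity. For an active event most of this stands, as Step 5 shows. For a resolved event it does not: the timing of the decrease rule says when a cut may be made, not whether a later increase is barred. An investigator who held back would be departing from a mandatory instruction.

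Four stronger readings are tempting, and the documents do not support them.

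- *Monitoring.* A reader might note that Section 10.4 schedules no safety laboratory test between Weeks +4 and +8, and infer that a neutropenic child could reach the Week +8 decision with no count since the cut. But the stop rule cannot be applied to neutropenia without a count about 2 weeks after the cut, and Section 13.3 requires each event to be followed to resolution or stabilisation. That sequence would mean the protocol had not been followed.
- *Size of the step.* A reader might quote 200 / 50 = 4 times or 200 / 25 = 8 times. The arithmetic is right, but the relevant comparison for safety is the dose at which the event arose, and there the step is at most 2 times.
- *Endpoint.* A reader might say that a reduced child is miscounted as needing escalation without 8 weeks at 100 mg. Section 9.1 specifies only an 8-week treatment period, so counting that child agrees with its wording.
- *Week +16.* A reader might claim the same defect there with equal force. The worked example for that path starts from a child for whom "then the dose stays at 100 mg SC daily"; the rule paragraph does not state that premise. The gap exists only on one reading.

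**Conclusion.** The point holds for the Week +8 rule. Followed as written, Section 27.7 orders a child who was reduced or restarted for a qualifying event, whose event has resolved, and who misses the MCID, to as much as twice the dose at which the event arose: 2.0 times at 25 kg or more, 1.6 times at 20 kg, 1.2 times at 15 kg. This assumes the event arose at 100 mg, which is the protocol dose for all but severely renally impaired patients before Week +8. It does not depend on whether the trigger means that either chosen outcome or both failed to improve, since the gap is present on both readings.

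The number of children affected is unknown. A reader might multiply the 5% to 15% in Section 12.3 by 20 and expect 1 to 3 children. Those percentages illustrate the precision of an estimated event rate and are not a forecast of dose-reducing events before Week +8. Only children who also miss the MCID would be affected, so the count could be zero.

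The point should be fixed: the group may be small, but the consequence concerns safety and the correction is simple.

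**What to change.** Add to both escalation paragraphs of Section 27.7, and cross-refer from Section 9.1:

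*The decrease, stop and restart rules take precedence. Escalation requires review of AEs and current safety labs. A subject with an ongoing qualifying AE, or whose dose was decreased, held or restarted for one, is not escalated automatically; any increase is a documented investigator decision made after the AE has resolved.*

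Placing it in the Week +16 paragraph as well keeps the two rules consistent and removes the doubt about that path.

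The cost is one short statement used twice and a cross-reference. AE review and safety labs are already scheduled at Weeks +8 and +16, so no visit or test is added. The drawback is that some children with mild, fully resolved events may be escalated later or not at all, and an increase may have to wait for a laboratory result.

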## 9.0 Study Endpoints

### 9.1 Primary and secondary endpoints.

#### Primary endpoints:

Phase 1: Incidence of treatment-emergent adverse events and laboratory values over 8 weeks of treatment to known frequency of anakinra-related AEs in other populations.

Phase 2: Need for dose escalation as determined by within individual change over 8-week treatment period compared to change over 8-week observational period in the 2 most bothersome symptoms for each enrolled patient, selected from measures for the MDRI. Choices are below in bold. These 2 symptoms will be monitored by one or more of the assessments below. If the Minimal Clinically Important Difference (MCID) that is defined below is not achieved after 8 weeks of treatment, or there has been a decrease of more than the MCID between 8 and 16 weeks after an increase greater than MCID at week 8, the dose will be escalated (see Section 27.7). If the MCID is not achieved after 8 weeks on maximum trial dose of 200mg (max dose 8 mg/kg/day), treatment with anakinra may be discontinued (see Section 27.7).

- Sanfilippo **Behavior** Rating Scale (SBRS): MCID = 0.25 SD for each scale
  - Symptoms described in table below:

|                         |                                                                                                                                        |                           |
|-------------------------|----------------------------------------------------------------------------------------------------------------------------------------|---------------------------|
| Body Movements          | Makes large complex movements of their body, such as spinning, twirling or repeatedly bouncing up and down.                            | Movement                  |
| Object Interaction      | Examines or manipulates some novel or unfamiliar objects repeatedly.                                                                   |                           |
| Activity/Routines       | Never plays with one object or engages in one activity for very long.                                                                  |                           |
| Emotional Function      | Expresses emotions inappropriate to the situation.                                                                                     | Social/emotional function |

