| Eye Contact             | Makes effort to avoid other people's gaze (keeps head down, looks away, or turns away).                                                |                           |
| Social Interaction      | Participates in group activities.                                                                                                      |                           |
| Emotional Engagement    | Doesn't seem to recognize or respond to other people's emotion.                                                                        |                           |
| Comfort Seeking         | Actively seeks comfort from familiar people.                                                                                           | Lack of Fear              |
| Safety Consciousness    | Is less aware of danger around the house (e.g. would touch hot oven) on the street or in the playground than other children their age. |                           |
| Fearfulness             | Is less fearful of new strange or scary things than other children of same age.                                                        |                           |
| Attention               | Is easily distracted                                                                                                                   | Executive function        |
| Self-Control/Compliance | Is impulsive, can't stop self.                                                                                                         |                           |
|                         |                                                                                                                                        |                           |
| Orality                 | Puts everything in their mouth; eats inedible things.                                                                                  |                           |
| Mood/Anger/Aggression   | Mood is irritable and cranky.                                                                                                          |                           |
| Self-Gratification      | Rubs genitals with hands, inside or outside clothing                                                                                   |                           |

- Child **Sleep** Health Questionnaire (CSHQ): MCID = 1-point change on the CSHQ Total score 

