- Autism **Parenting Stress** Index (APSI): MCID = 0.25 SD for Stress Total 
  - Ability to communicate
  - Tantrums/meltdowns
  - Self-injurious behavior
  - Difficulty making transitions from one activity to another
  - Toilet training
  - Not feeling close to your child
  - Concern for your child not being accepted by others
  - Concern for the future for your child living independently
- PROMIS **Fatigue** - Parent Proxy Custom Short Form: MCID = 3-point change
- **Seizures** – Parents will record each seizure in a seizure journal provided by the study. Information recorded will include the duration (average length of seizure), and need for medical intervention (e.g. rescue medication, medical evaluation).

- **Movement** disorder (e.g. dystonia, chorea, etc.) – Parent reported duration and severity. Change in one of two characteristics for +/-1 score, +/-2 score for change in two of the characteristics.
- Non-communicating Children's **Pain** Checklist-Revised (NCCPC-R): MCID = 0.25 SD

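### The Week +8 escalation rule leaves out the observational-period comparison that defines the Phase 2 primary endpoint, so the raw proportion escalated cannot show whether the starting dose is adequate

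*Protocol*

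**What the plan says.** Protocol 9.1 defines the Phase 2 primary endpoint as "Need for dose escalation as determined by within individual change over 8-week treatment period compared to change over 8-week observational period" in each child's two most bothersome symptoms. It then gives the trigger only as the MCID that "is not achieved after 8 weeks of treatment", without saying whether one or both symptoms must fall short. It adds that "These 2 symptoms will be monitored by one or more of the assessments below", without saying how several assessments of one symptom combine.

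The thresholds in 9.1 are:
- SBRS: "MCID = 0.25 SD for each scale".
- APSI: "MCID = 0.25 SD for Stress Total".
- NCCPC-R: also 0.25 SD.
- CSHQ: "MCID = 1-point change on the CSHQ Total score".
- PROMIS Fatigue: 3 points.
- Movement disorder: its own score of plus or minus 1 or 2.

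Protocol 27.7 raises the dose at Week +8 if "at least one of the two most bothersome outcomes selected by the parents/guardians at the Day 1 visit has not improved by" the MCID. The worked example in the same section reads "if a subject has not improved in the chosen items then the dose will be increased to 200 mg SC daily", which could mean either or both. The Week +16 text has the same conflict: the rule needs at least one outcome to worsen, while the example speaks of both.

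Protocol 12.2 names McNemar and Wilcoxon signed rank tests for changes between the two periods. It does not apply them to the escalation classification.

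**The concern.** The 8-week observational period is the only untreated reference in this single-arm trial. Section 9.1 brings it into the primary endpoint, but the operative rule in 27.7 does not use it. What remains is a before/after change in two caregiver-rated scores, cut at a threshold that may be small relative to visit-to-visit variation.

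The stake is the meaning of the Phase 2 result. Section 3.0 says that change in the MDRI informs dose-finding by reflecting lack of clinical change. If most children are escalated, the natural conclusion is that the starting dose is inadequate. That conclusion is unsafe if the rule also escalates most children when the dose delivers the protocol's own minimal benefit. It is equally unsafe in the other direction if, on the alternative reading, many untreated children would count as improved.

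**Working it through.** The protocol gives no expected escalation rate for this rule, so there is no stated figure to reproduce.

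**Inputs**
- From the protocol: threshold 0.25 SD (9.1), two outcomes per child (9.1, 27.7), n = 20 (6.0).
- Assumed: test-retest correlation r = 0.5 to 0.9. The protocol gives reliability only for the VABS-III (0.76 to 0.98, section 10.16), which is not an MDRI component.
- Assumed: correlation between the two changes of 0 to 0.6, and normally distributed changes.

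**Formulas**, in SD units with true mean improvement d:
- SD of a change = √(2(1 − r)), which is 1.0 at r = 0.5 and 0.45 at r = 0.9.
- Chance that one outcome reaches the MCID: q = Φ((d − 0.25)/√(2(1 − r))).
- Literal 27.7 rule, independent outcomes: P(escalate) = 1 − q².
- Alternative reading (escalate only if neither improves): P(escalate) = (1 − q)².
- Correlated changes: bivariate normal in place of the products.

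**At one MCID.** With d = 0.25, q = Φ(0) = 0.5 at every r, so the literal rule gives 1 − 0.5² = 75%. This needs no reliability assumption. With correlation 0.6 it is about 65%.

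**Worked case, r = 0.7, independent outcomes** (SD of change √0.6 = 0.775):
- d = 0: q = Φ(−0.323) = 0.373; literal 1 − 0.373² = 86%; alternative 0.627² = 39%.
- d = 0.5: q = Φ(0.323) = 0.627; literal 1 − 0.627² = 61%; alternative 0.373² = 14%.

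**Full range** (r 0.5 to 0.9, correlation 0 to 0.6):

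| True mean improvement | Literal 27.7 rule | Escalate only if neither improves |
|---|---|---|
| None | 74% to 92% | 36% to 59% |
| One MCID | 65% to 75% | 25% to 35% |
| Twice the MCID | 41% to 64% | 8% to 26% |
| Three times the MCID | 21% to 52% | not tabulated |

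On the alternative reading, the share of children on an inert drug who count as improved is 100% minus the first row: 41% to 64%.

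**In 20 children.** Under the literal rule at r = 0.7 with independent outcomes, the binomial 95% range of the number classed is 14 to 20 with no effect (p = 0.861) and 8 to 16 at twice the MCID (p = 0.607). The ranges overlap. At twice the MCID, 11 or more of 20 are still classed as needing escalation in about 78% of trials.

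**CSHQ.** If the score SD is 5 to 10 points and r is 0.6 to 0.9 (both assumed), the SD of change is 2.2 to 8.9 points, and a 1-point gain occurs by chance in 33% to 46% of children.

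**What the untreated window adds.** For one outcome, the difference of changes (Week +8 minus Day 1) minus (Day 1 minus Week -8) has SD √(6(1 − r)). Averaged over two independent outcomes at r = 0.7, this is √(1.8/2) = 0.95. With d = 0.5 and n = 20 the standard error is 0.95/√20 = 0.21, a ratio of about 2.4 and a power of about 61%. In simulation at the same settings, the rule's rate was 60.7% on treatment and 86.1% in the observational window. The paired test of the classification (exact McNemar) had about 26% power; the large-sample form does somewhat better but stays well below 61%.

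**The case against.** A reader might infer that the rule fires in most children whether or not the starting dose works. The figures do not support that. At three times the MCID the literal rule escalates 21% to 52%. With independent outcomes and r from 0.6 to 0.95 it falls below half once the true effect exceeds about 0.42 to 0.74 SD. Escalating children for whom the dose does nothing is also the rule's purpose, not a fault.

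A reader might also blame the small MCID for the high rate. That is wrong. At r = 0.7 with no effect, a threshold of zero gives 75% and 0.25 SD gives 86%, so a smaller threshold lowers escalation. The high rate comes from requiring both outcomes to improve; the noise is what weakens discrimination. The 75% at one MCID would hold for any threshold that the true mean change just meets.

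Nor do the high rates survive every reading: on the neither-improved reading most treated children are not escalated.

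The reliabilities are assumed. The model also leaves out regression to the mean, unblinded caregiver optimism and several assessments per symptom, which could lower escalation, and disease progression, which would raise it. PROMIS Fatigue and movement disorder are not modelled.

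Finally, nothing in the protocol says the raw proportion will be read as a verdict on the starting dose. Section 9.1 already promises the period comparison, and 12.2 already lists paired tests.

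All of this stands and limits the claim. It does not remove the mismatch between 9.1 and 27.7, which is fixed in the protocol text and is not a detail left to an analysis plan.

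**Conclusion.** The concern holds in limited form. The mismatch rests on no assumption: 9.1 determines need for escalation by comparison with the observational period, and 27.7 classifies children without it. The passages also disagree or are silent on whether one or both outcomes must fall short.

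Under the literal rule, 65% to 75% of children are classed as needing escalation when the dose delivers exactly the MCID on average in both outcomes. This depends only on how strongly the two changes correlate (0 to 0.6). The remaining rates rest on assumed reliabilities of 0.5 to 0.9. They show a rule that separates large effects from none but not modest effects in 20 children. On the alternative reading the error reverses, and many children on an inert drug count as improved.

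On either reading the raw proportion escalated, taken alone, does not measure whether the starting dose is adequate. This should be corrected. It does not invalidate the study, because the reference data are already being collected.

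**What to change.** - **Reconcile the text.** The sponsor should align 9.1, the rule in 27.7 and the worked examples on whether one or both outcomes must fall short, and on whether the observational change enters the rule. No dosing rule is proposed here.
- **Add the reference.** In 9.1 and 12.2, state that the raw proportion escalated will not be interpreted alone. Apply the same reconciled classification to the same two outcomes over Week -8 to Day 1, and report the paired difference in proportions with a 95% CI.
- **Add the continuous contrast.** Report (Week +8 minus Day 1) minus (Day 1 minus Week -8) per child, in MCID or SD units for the scaled measures, with movement disorder kept on its own score. The movement diary starts at Week -6 (10.2, footnote h), so its reference window is shorter; say so.
- **State the selection bias.** The two outcomes are chosen at Day 1, so regression to the mean can favour the treatment window. Treat the contrast as descriptive unless this is handled, for example by a sensitivity analysis over all MDRI components.
- **Do not write in a fixed no-effect rate.** It depends on the reading and on unknown reliabilities; the observed Week -8 to Day 1 rate serves as the reference.

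The cost is wording and analysis only, since both windows are already measured. The downside is that the dose-finding result becomes less clear-cut.
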